## 2. Patients and Methods

### 2.1. Setting

We conducted a multicenter, randomized, single‐blind, controlled clinical trial across three centers in China: LongHua Hospital Shanghai University of Traditional Chinese Medicine, Shanghai Gongli Hospital of Pudong New Area, and Shanghai Municipal Hospital of Traditional Chinese Medicine, Shanghai University of Traditional Chinese Medicine. We will recruit participants and conduct treatment in these three hospitals. Ethical approval was obtained from the Medical Ethics Committee of LongHua Hospital Shanghai University of Traditional Chinese Medicine (No. 2024LCSY150), Shanghai Gongli Hospital of Pudong New Area (GLYY1s2024‐085), and Shanghai Municipal Hospital of Traditional Chinese Medicine (2025SHL‐KY‐60‐01), and the study was registered with the International Traditional Medicine Clinical Trials Registry. A total of 120 MRM participants will be recruited for this trial and assigned to the electroacupuncture or sham electroacupuncture groups in a 1:1 ratio. The recruitment period will be from December 2024 to May 2027. A flowchart of the trial procedure is shown in Figure 1. This study adheres to the Declaration of Helsinki.

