## 3. Outcomes

At baseline, basic information about the participants will be collected, including age, body mass index (BMI), duration of migraine, accompanying symptoms of migraine (nausea, vomiting, photophobia, and phonophobia), and medication history. A 28‐week headache diary needs to be kept (including a 4‐week baseline period, 12‐week treatment period, and 12‐week follow‐up period). The headache diary will record daily frequency, time, location, VAS score, and associated symptoms of migraine as well as medications taken and menstrual periods. The schedule of enrollment and assessment is shown in Table 2.

**TABLE 2 tbl-0002:** Schedule of enrollment, interventions and assessments.

Study period		Enrollment	Intervention period			Follow‐up period
Time point		Weeks −3–0	Weeks 1–4	Weeks 5–8	Weeks 9–12	Weeks 13–24

Eligibility screening		×				

Sign informed consent		×				

Medical history		×				

Randomization		×				

Intervention						

Electroacupuncture			×	×	×	

Sham electroacupuncture			×	×	×	

Primary outcomes (vs. baseline)						

Migraine days and attacks during Weeks 9–12					×	

Secondary outcomes (vs. baseline)						

Frequency‐related	Migraine days/attacks per 4 weeks (Weeks 1–24, excluding Weeks 9–12)		×	×		×
	Migraine days/attacks per 4 weeks (during menstrual/nonmenstrual periods)	×	×	×	×	×

Symptom characteristics	Days/attacks with migraine‐associated symptoms, and attack duration per 4 weeks	×	×	×	×	×

Patient‐reported	VAS	×	×	×	×	×
	MIDAS	×			×	
	ISI	×			×	
	GAD‐7	×			×	
	PHQ‐9	×			×	

Others	Treatment response rate (the proportion of patients with ≥ 50%, 75%, or 100% reduction per four weeks of migraine days)		×	×	×	×
	Average dosage and frequency of emergency drugs	×	×	×	×	×

Adverse events			×	×	×	×

Success of blinding					×	

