## 4. Sample Size Calculation

This study was a multicenter, randomized, single‐blind, controlled clinical trial, in which the primary outcome was migraine days and attacks during Weeks 9–12 vs. baseline. According to the preliminary test results derived from an internal, unpublished pilot observation conducted by our research team between April 2024 and August 2024, which involved 15 participants in each group, of the research group, the mean and standard deviation of migraine days in the electroacupuncture group and the sham electroacupuncture group were 3.13 ± 1.77 and 1.98 ± 1.46, respectively. The mean and standard deviation of migraine attacks in the electroacupuncture group and sham electroacupuncture group were 2.13 ± 1.12 and 1.17 ± 1.20, respectively. Setting the ratio of the electroacupuncture group to the sham electroacupuncture group as 1:1, the test level *α* = 0.05 (bilateral), and power (1−*β*) = 0.90, the sample size of each group was calculated to be 51 cases. Considering a shedding rate of 15%, 60 cases will be taken in each group and 120 cases in total.

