## 5. Randomization

The study will use the block randomization method. Each center competes to be included in the group. The random scheme for the study is generated by the “Proc plan” program of SAS 9.4 statistical analysis software, and the random distribution cards are made, which are sealed with an opaque envelope. The envelope serial number is the same as that of the card. The envelope will be opened in the order of visits by participants. The corresponding researchers at each center will randomly assign participants into two groups based on the contents of the envelope card in a 1:1 ratio: eligible participants to the electroacupuncture group or the sham electroacupuncture group.

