## 7. Analysis

Data collection and entry for this study will be conducted by specially trained clinical staff. Efficacy analyses will be performed on both the intention‐to‐treat (ITT) population and the per‐protocol set (PPS) population. Missing values for patients in each group will be imputed using the last observation carried forward (LOCF) method. The safety analysis set (SAS) will be analyzed within the ITT population, which includes all randomized subjects who received at least one treatment.

Given that additional acupoints are selected based on the specific location of headache during acute attacks, we will quantitatively report the percentage of patients in each subgroup and compare baseline characteristics and changes in primary outcomes across subgroups.

SAS software (Version 9.4; SAS Institute Inc., Cary, North Carolina 27513, US) will be used for the statistical analysis. Qualitative data will be described as cases and percentages, and quantitative variables will be described as mean, median, standard deviation, and quartile range. Statistical significance was set at *p* < 0.05.

The primary outcome of this study was migraine days and attacks during Weeks 9–12 vs. baseline. The data will be recorded in a headache diary and analyzed using two independent sample *t*‐tests or rank‐sum tests. For the analysis of secondary outcomes, two independent sample *t*‐tests or rank‐sum tests were used for quantitative data, and the chi‐square test or Fisher’s exact test will be used for qualitative data. Data obtained from repeated measurements will be statistically analyzed using generalized estimating equations. The chi‐square test will also be used for a safety indicator.

The headache diary in this study involved multiple data collections. If participants complete the headache diary for at least 28 days in consecutive 4‐week periods, researchers will directly calculate the number of migraine days per month. If the number of days that participants complete the headache diary in consecutive 4 weeks is less than 20, monthly migraine days will be classified as missing. Missing days will be defined as days in which participants do not complete the evening report and do not report headaches. Estimation over 4 weeks will be used for missing data, using the number of migraine days within four weeks divided by the number of days observed during four weeks multiplied by 28 as the monthly score for the four weeks.

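### The primary comparison is an unadjusted t-test or rank-sum test; a single model adjusted for the baseline 4-week count would give more precision from data already collected

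*Protocol article*

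**What the plan says.** All places are in the protocol article.

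- **Endpoint (7. Analysis):** "The primary outcome of this study was migraine days and attacks during Weeks 9–12 vs. baseline".
- **Test (7. Analysis):** "The data will be recorded in a headache diary and analyzed using two independent sample" t-tests or rank-sum tests. The article names no covariate and no rule for deciding between the two tests.
- **Repeated measures (7. Analysis):** after the sentence on secondary outcomes, "Data obtained from repeated measurements will be statistically analyzed using generalized estimating equations".
- **Baseline data (3. Outcomes):** the headache diary runs for 28 weeks, "including a 4‐week baseline period, 12‐week treatment period, and 12‐week follow‐up period". A baseline 4-week count is thus collected in the same way as the Weeks 9–12 count.
- **Centres (2.1. Setting; 5. Randomization):** three centres. "The study will use the block randomization method. Each center competes to be included in the group". Stratification by centre is not stated.
- **Covariates elsewhere (9. Discussion):** covariate analyses are mentioned only as a way to deal with emergency medication.

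**The concern.** The outcome is a count over four weeks, and the same count is recorded before treatment. Entry allows an average of 2 to 8 attacks a month, so patients can start from quite different levels. Where the baseline count predicts the later count, adjusting for it removes noise from the treatment comparison. Subtracting it removes some of that noise but in general not the optimal amount, because subtraction forces a slope of 1 on baseline whatever the data show. A change score also over-corrects a chance baseline difference between the groups when the true slope is below 1.

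The second element is the word "or". A t-test targets a difference in mean days or attacks; a rank-sum test targets a shift in ranks. The article does not say which of them carries the conclusion for each primary endpoint.

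At stake are the width of the primary confidence interval, the margin if the true effect is smaller than the pilot suggested, and clarity about which result is primary.

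**Working it through.** **Inputs from 4. Sample Size Calculation.** Pilot migraine days: 3.13 (SD 1.77) with electroacupuncture and 1.98 (SD 1.46) with sham, 15 patients per group. Two-sided alpha 0.05, power 0.90, 51 per group, 60 after 15% dropout.

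Difference = 3.13 − 1.98 = 1.15 days. Pooled SD = √[(1.77² + 1.46²)/2] = 1.622.

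**Step 1. How baseline enters.** The endpoint is defined against baseline. The pilot means are higher under electroacupuncture, which fits a hypothesised benefit only if they are reductions. I therefore take the planned test as a comparison of change scores and 1.622 as the SD of the change.

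**Step 2. The plan's own figure.**
- n = 2(1.960 + 1.282)² × SD²/1.15².
- With the pooled SD this gives 42 per group (43 by the t distribution).
- With SD 1.77 it gives 50 (51 by t). The pooled SD at alpha 0.025 also gives 50 (51 by t).
- The stated 51 is thus reproducible for days under either of the last two settings; the article does not say which was used.
- 51/0.85 = 60 reproduces.

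**Step 3. Variance ratio.** Let baseline and follow-up have common variance σ² and correlation r.
- Change score: 2σ²(1 − r)
- ANCOVA: σ²(1 − r²)
- Ratio: (1 − r²)/[2(1 − r)] = (1 + r)/2

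The article gives no r, so I use an assumed range of 0.3 to 0.7.

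| r | Variance ratio | 51 per group performs like |
|---|---|---|
| 0.3 | 0.65 | 51/0.65 = 78 |
| 0.5 | 0.75 | 51/0.75 = 68 |
| 0.7 | 0.85 | 51/0.85 = 60 |

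**Step 4. Power for migraine days.** Noncentral t, 51 per group, two-sided alpha 0.05, SD = 1.622 × √ratio. The 0.8-day difference is my assumption.

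| True difference | Change score | ANCOVA, r = 0.7 | r = 0.5 | r = 0.3 |
|---|---|---|---|---|
| 1.15 days (pilot) | 94.3% | 97.0% | 98.4% | 99.3% |
| 0.8 days (assumed) | 69.4% | 76.3% | 81.3% | 86.4% |

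**Step 5. Why look below 1.15 days.** The standard error of the pilot difference is 1.622 × √(2/15) = 0.592. With t(28) = 2.048, the 95% interval is 1.15 ± 1.21, or −0.06 to 2.36 days. A true difference of 0.8 lies well inside it.

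**Step 6. Migraine attacks.** Difference 2.13 − 1.17 = 0.96; pooled SD = √[(1.12² + 1.20²)/2] = 1.161. The change-score test at 51 per group already has 98.5% power, so on the pilot figures adjustment has little left to add for this endpoint.

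**Not computed.** The gain from adding centre, because no between-centre variance is given.

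**The case against.** The best defence is that nothing here is invalid. Under randomisation an unadjusted comparison of change scores is unbiased and holds its error rate. At the plan's own 1.15 days it exceeds the 90% target, and adjustment adds only about 3 to 5 percentage points. The larger gain rests on a 0.8-day effect that appears nowhere in the article. The correlation and the equal-variance condition are also assumed, and no baseline SD is given. All of this stands, and it limits the point to precision. With unequal variances the ratio differs from (1 + r)/2, but in large samples ANCOVA still does no worse than the change score.

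A reader might infer more than the document supports:

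- **That the baseline count is thrown away.** The endpoint wording and the direction of the pilot means indicate a change score, so baseline is used, though inefficiently.
- **That the test will be picked after seeing the results.** The article is silent on the rule, an analysis plan not shown may contain one, and 6. Blinding says the statistical analysts are blinded and a third party does the analysis. In a simulation of skewed null data, taking the smaller of the two p-values gave about 6.9% false positives, but the article proposes no such procedure.
- **That the generalized estimating equations are a rival primary analysis.** That sentence follows the secondary outcomes, and the secondary frequency outcome excludes Weeks 9–12.
- **That leaving out centre contradicts the design.** Stratification by centre is not stated, so no mismatch is shown.
- **That a rank-sum result cannot be expressed in days.** A Hodges-Lehmann shift can be reported.

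**Conclusion.** The point holds as an improvement in efficiency and clarity. The stated primary test is unadjusted and uses the baseline count, as far as the text shows, only by subtraction. An ANCOVA on the same data would have 15% to 35% less variance if r lies between 0.7 and 0.3 and the variances are equal. For migraine days this lifts power from about 94% to 97–99% at the pilot difference, and from 69% to 76–86% if the true difference is 0.8 days. The figures also rest on reading the pilot values as reductions from baseline.

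The trial should not be called underpowered or its test invalid on this ground. Naming two tests without saying which governs is a lesser defect that the same change resolves.

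**What to change.** For each primary endpoint (days and attacks), prespecify one model: the Weeks 9–12 count on treatment and the baseline 4-week count, fitted by ANCOVA with robust standard errors. Centre may be added as a covariate. Report the adjusted mean difference with its 95% confidence interval as the primary result. Keep the rank-sum test as a named sensitivity analysis, so that a single test governs the primary conclusion for each endpoint.

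The cost is a change of wording in the protocol's Analysis section and in any statistical analysis plan, made before unblinding. Baseline counts and centre are already recorded, and the sample size need not change.

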## 8. Data Collection, Management, and Monitoring

In this study, the designated researchers will use the preestablished CRF to collect the participants’ basic information and clinical data. Prior to the clinical trial, all personnel involved in data collection will receive standardized training on data collection, entry, and management. The double‐entry method will be used to ensure data accuracy. To avoid discrepancies, the data will be entered independently by two researchers, followed by data verification. Besides, a data safety monitoring team has been established for the trial’s performance and safety, which is mainly composed of experts from mainland China. Data management follows the specified schedule, procedures, and guidelines outlined in the data management plan. The CRF, informed consent, and other materials will be archived by the LongHua Hospital Shanghai University of Traditional Chinese Medicine.

## 9. Discussion

MRM is characterized by intricate physiological and pathological mechanisms, resulting in more severe clinical manifestations and prolonged duration compared to non‐MRM. The cyclic recurrence of MRM increases patients’ reliance on analgesic medications, possibly increasing their susceptibility to drug tolerance [30]. This recurrent nature significantly affects patients’ physical and mental health [7], diminishes their quality of life [6], and imposes economic burden due to missed work [31]. Consequently, the implementation of prevention and treatment strategies is critical to improve the prognosis of patients with MRM. However, the adverse reactions associated with acute and preventive pharmacotherapy, along with the risk of overdose migraines due to frequent medication use, render long‐term drug therapy a concern that cannot be overlooked [12]. Therefore, there is an urgent need to develop safe and effective alternative treatment options.

The clinical efficacy of acupuncture in the treatment of migraine has been substantiated in numerous RCTs [32]; however, related research is limited regarding its effectiveness, specifically for MRM. This study was designed to address the unique characteristics of MRM and proposes an EA intervention. MRM is closely linked to the menstrual cycle, particularly during premenstrual and menstrual phases. Accordingly, our intervention included two treatments in the premenstrual and menstrual weeks, along with one treatment in each of the other 2 weeks. This approach not only enhances the specificity of treatment but also reduces the time burden on patients. The location of migraine attacks is another critical factor in electroacupuncture treatment. Thus, during acute migraine phases, supplementary acupoints are chosen based on the location of pain to optimize treatment effectiveness. In addition to acupoint selection, the choice of electrical stimulation parameters is equally important. Previous studies have shown that alternating stimulation at 2 and 100 Hz using a sparse‐dense wave can simultaneously activate the enkephalin and dynorphin systems, producing a stronger synergistic analgesic effect than single‐frequency stimulation [33]. Furthermore, a randomized controlled trial involving 90 patients with migraine confirmed that variable‐frequency (2/100 Hz) electroacupuncture exhibited superior clinical efficacy compared with low‐frequency (2 Hz) or high‐frequency (100 Hz) electroacupuncture in the treatment of migraine [34]. Taken together, these findings provide a solid physiological and clinical rationale for using the 2/100 Hz alternating sparse‐dense wave protocol in the present trial. Furthermore, to bolster the reliability of our study, both electroacupuncture and sham electroacupuncture treatments will utilize the same auxiliary device (patent number: ZL 2023 20605629.3). This strategy not only facilitates blinding but also encourages patient adherence to treatment. Previous clinical studies have confirmed the feasibility of placebo application [35].

However, this study had certain limitations. To adhere to medical ethical standards, the patients were permitted to use emergency medications during the study period, which may have influenced the assessment of therapeutic efficacy. To mitigate this impact, we conducted subgroup and covariate analyses. Additionally, because of the unique nature of acupuncture techniques, the acupuncturists could not be blinded in this study.

In conclusion, high‐quality clinical studies investigating the efficacy and safety of electroacupuncture for MRM are essential. We anticipate that the results will provide clinical evidence for the use of electroacupuncture in the treatment of MRM, ultimately enhancing the clinical symptoms and quality of life of patients.

## Patient Perspective

Patients and/or the public were not involved in the design, conduct, reporting, or dissemination plans of our research.

## Data Availability

Data sharing does not apply to this article as no datasets were generated or analyzed during the current study.
